### Interventions

VMMC is the intervention to be evaluated in this study. Men in the intervention group will undergo VMMC within 3 months of randomization, and they could choose one of 2 types of circumcision (disposable circumcision stapler surgery and conventional surgical procedure), while those in the control group will remain uncircumcised during the follow-up. All men will be followed for 12 months.

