### Randomization and Follow-Up

Eligible men will be randomized using a 1:1 allocation ratio to the intervention and control groups. Randomization lists for each study site have been pregenerated by researchers. Each envelope with a unique number will be assigned for 1 allocation sequence, into which a card with grouping information will be put before sealing. Trained investigators at each study site will assign an envelope to each participant according to the order of the participant’s arrival. Participants cannot be blinded due to the nature of the intervention. After randomization, trained researchers will provide HIV prevention counseling to participants in both groups, including promotion of consistent condom use and regular HIV testing.

Participants randomized to the intervention group will be encouraged to complete VMMC within 1 week of enrollment. Time to VMMC can be extended up to 3 months after enrollment on a case-by-case basis. We recommend participants to undergo VMMC at a secondary or higher-level medical center of their own choice. Although the clinical VMMC activities are not part of study procedures, a research assistant would accompany the participants to the hospital to undergo the circumcision. This trial will provide a surgical subsidy of CNY 1000 (US $160). If participants do not complete VMMC within 1 month of enrollment, a text message reminder will be sent. The surgeon will check the condition of the foreskin of participants before the operation to determine if surgery is necessary. Men in the intervention group will be advised to abstain from sex for 6 weeks after undergoing VMMC, and the 12-month follow-up period will begin after this 6-week period of abstinence. If men resume sexual behaviors earlier than 6 weeks after VMMC, then the 12-month follow-up period will begin at the time of their first sexual encounter after VMMC.

Men randomized to the control group will complete the baseline survey after enrollment. The 12-month follow-up period for the control group will begin immediately after completing the baseline survey. At the end of the 12-month follow up period, men in the control group will be offered a CNY 1000 (US $160) subsidy to undergo VMMC.

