### Sample Size

The sample size is calculated based on the supposed protective rate of circumcision. Studies have shown that HIV incidence among MSM was 12.5/100 person-years in Chongqing [26], 15.5/100 [27] and 10.3/100 person-years [28] in Shenyang, and 15.6/100 person-years in 8 cities in China [29]. Considering participants in the CoM Study predominantly practiced insertive anal sex, consequently with lower HIV infection risk compared with those who primarily practiced receptive role, and that the effect of VMMC may be higher among men who primarily or exclusively practice the insertive anal intercourse than MSM overall, we suppose HIV incidence among MSM to be 10/100 person-years and protective rate of circumcision to be 80%, and thus, HIV incidence would be 2/100 person-years in the intervention group. A target sample size of 240 (120 in each group) is set to achieve 80% power at 1-sided α=.10, with 10% lost to follow-up.

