### Statistical Analysis

All data will be analyzed based on the principle of intention to treat. We will assess the type of missing data and assess attrition effects by testing whether there are systematic differences between dropouts and nondropouts. Key baseline characteristics will be examined between the intervention and control groups to ensure they are balanced; if not, subsequent analyses will assess whether these characteristics are confounding factors of the intervention.

For continuous variables, we will calculate means and SDs, and means will be compared with 2-sample *t* tests or Mann-Whitney tests. For categorical variables, proportions will be compared with chi-square tests or Fisher exact tests. In addition, we assume that HIV status at the end of follow-ups is grouped censored data and suitable for exponential, proportional hazards model with constant baseline hazard. Therefore, differences between the intervention and the control groups will be identified with a Poisson regression model, which includes observed covariates (ie, HIV risk behaviors, such as condom use, number of sexual partners, frequency of insertive anal sex, and HIV-positive sexual partners as well as demographic variables, such as age, education level, and income). Incidence rates will be calculated for each outcome in the 2 groups. Moreover, the incidence rate ratios and their 95% CIs will be estimated using the Poisson regression model. For all the outcome variables, including the primary (ie, HIV incidence) and secondary (ie, penile HPV incidence, clearance and persistent infection, HSV-2 incidence, and syphilis incidence) outcomes of interest, the aforementioned analyses will be repeated across all the visits (ie, 6- and 12-months follow-ups).

The changes in sexual behaviors after VMMC over time between the intervention and the control groups will be compared with the generalized estimating equations. For outcomes of VMMC safety and satisfaction among circumcised MSM, we will perform the same statistical description and comparative analyses described as above.

A 2-sided *P* value lower than .05 will be used to infer statistically significant difference. All the statistical analyses will be performed with R software (version 4.2.1; R Core Team).

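### A Poisson regression with at least seven covariates is planned on about 13 expected infections; with ordinary Wald inference it would report a zero-infection VMMC arm as null

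*Protocol article*

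**What the plan says.** In Sample Size, the article writes "we suppose HIV incidence among MSM to be 10/100 person-years" for the control rate and adds that "HIV incidence would be 2/100 person-years in the intervention group", an 80% reduction. It continues: "A target sample size of 240 (120 in each group) is set to achieve 80% power at 1-sided α=.10, with 10% lost to follow-up". Men are "randomized using a 1:1 allocation ratio to the intervention and control groups" (Randomization and Follow-Up), and follow-up is 12 months (Interventions).

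In Statistical Analysis, "differences between the intervention and the control groups will be identified with a Poisson regression model, which includes observed covariates". Seven covariates are named: condom use, number of partners, frequency of insertive anal sex, HIV-positive partners, age, education and income. For the effect measure, "the incidence rate ratios and their 95% CIs will be estimated using the Poisson regression model". Significance is judged at 2-sided .05, and the analyses are repeated at 6 and 12 months. Fisher's exact test is named, but only for proportions of categorical variables. The section does not say whether the Poisson tests and intervals are Wald, likelihood-based or exact.

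**The concern.** Standard inference from a Poisson regression relies on large samples, and this design expects very few events. The effect the trial is powered for is so large that an empty VMMC arm is a realistic result. When one arm has no events, the fitted log rate ratio runs to minus infinity and its standard error explodes. A Wald test then cannot reject, however many infections the control arm has, so the strongest result the trial could produce would be reported as no evidence of an effect. Seven or more covariates on about 13 events add to the instability. The choice of inference method can therefore decide the trial's conclusion, and it is best settled before the data are seen.

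**Working it through.** **The plan's own figure.** The log-rate-ratio (Wald) formula at 1-sided .10 and 80% power gives

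n = (1.282 + 0.842)² × (1/0.10 + 1/0.02) / (ln 0.2)² = 104.4, so 105 per arm; 105/0.9 gives 117 per arm, 234 in total.

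This is close to the stated 240. The pooled two-proportion formula matches 120 per arm exactly, but only at 1-sided .05 (108, then 108/0.9 = 120). The inputs are in any case consistent with about 108 evaluable men per arm.

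**Expected events.** Evaluable person-years per arm: 120 × 0.9 × 1 year = 108, with dropouts contributing no time.

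- Control: 108 × 0.10 = 10.8. VMMC: 108 × 0.02 = 2.16. Total: 12.96.
- Events per named covariate: 12.96/7 = 1.9. Counting the treatment term: 12.96/8 = 1.6. Multi-level education or income terms would lower this further.

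**Chance of no VMMC infection**, exp(−person-years × VMMC rate):

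| Scenario | Person-years per arm | P(0 in VMMC) |
|---|---|---|
| Design, dropouts give no time | 108 | exp(−2.16) = 11.5% |
| Dropouts give half their time (assumption) | 114 | exp(−2.28) = 10.2% |
| No loss | 120 | exp(−2.40) = 9.1% |
| 6-month repeat | 54 | exp(−1.08) = 34% |
| Rate ratio 0.44, 12 months | 108 | exp(−4.75) = 0.9% |

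The 0.44 comes from the 56% lower odds that the Introduction cites for mainly insertive men, used here as a rate ratio by assumption.

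**What a zero count does.** Take 11 control and 0 VMMC infections in 108 person-years each.

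- Wald from the Poisson model: standard error about 13,000, P = .999, 95% CI 0 to infinity.
- Likelihood ratio, same model: 2 × 11 × ln 2 = 15.25, P = .0001; profile upper limit exp(3.84/22) − 1 = 0.19.
- Mid-P conditional: P = 0.5¹¹ = .0005; upper limit 0.05^(−1/11) − 1 = 0.31.
- Exact conditional: P = 2 × 0.5¹¹ = .001; upper limit 0.025^(−1/11) − 1 = 0.40.

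**Power and size at 2-sided .05**, by enumerating independent Poisson counts with equal person-years and no covariates. The null columns put 10.8 or 6.48 expected events in each arm.

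| Test | Power, 10.8 vs 2.16 | Power, rate ratio 0.44 | Null rejection, 10.8 each | Null rejection, 6.48 each |
|---|---|---|---|---|
| Wald | 52% | 28% | 4.2% | 2.9% |
| Exact conditional | 61% | 25% | 2.9% | 2.5% |
| Mid-P conditional | 69% | 32% | 4.5% | 4.4% |
| Likelihood ratio | 76% | 36% | 5.4% | 6.4% |

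Under the design, trials with no VMMC infection that the exact test calls significant have probability 11.0%, nearly all of the 11.5%. Wald rejects in none of them. At the 6-month repeat (5.4 vs 1.08 expected), power is about 8% for Wald and 34% for mid-P.

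**With covariates.** In 1,500 simulated trials with seven null covariates (distributions assumed, yearly risks 1 − exp(−rate)), 11.1% had no VMMC event. The treatment standard error was degenerate in the same proportion, and Wald power was 49%.

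**The case against.** The strongest reply is that the article never says Wald. The type of interval and a fallback for a zero count are commonly left to a statistical analysis plan, and that plan is not shown. Their absence alone is therefore not a defect, and the damaging Wald figures are conditional. This stands. What remains is what the article does fix: a model with at least seven covariates for about 13 events, as the vehicle for the primary comparison and its interval.

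A reader might infer that the Poisson model itself yields nothing usable when the VMMC arm is empty. The article does not support that. The same model's likelihood-ratio test and profile interval stay informative (upper limit 0.19 for 11 vs 0), and a point estimate of zero would appear under any method because it reflects the data.

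A reader might also infer that a fully exact test is the natural remedy and recovers power across the board. It does not. Its advantage under the design comes from zero-event trials. With at least one VMMC infection it contributes 49.6 points of power against 52.2 for Wald, and mid-P contributes 58.1. At a rate ratio of 0.44 it is weaker than Wald (25% vs 28%), and its null rejection of about 3% is noticeably conservative.

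Finally, the 9-12% chance of an empty arm depends on 80% efficacy. With a more modest effect it nearly vanishes at 12 months. That is a fair limit on the size of the problem. But 80% is the effect for which the trial is powered, so the analysis should cope with the data that effect would produce.

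**Conclusion.** The concern holds in a conditional form, as a should-fix. The article commits the primary comparison to a large-sample model with under two expected events per covariate. If ordinary Wald output is used, the best possible result would be reported as null about one time in nine under the design hypothesis. At the same 2-sided .05, Wald power is about 17 points below mid-P and 23 to 24 points below the likelihood-ratio test, part of whose lead reflects its mild liberality. The shortfall of all four tests from the planned 80% is partly a separate matter, because the sample size was set at 1-sided .10.

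The figures assume the article's rates, 1:1 allocation, 12 months' follow-up and dropouts contributing no time. The power comparison is unadjusted.

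**What to change.** Add one sentence to the analysis plan before the data are analysed. The primary test and 95% CI should come from one of the following, with Wald P values and intervals excluded:

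- the mid-P conditional comparison of the two incidence rates; or
- likelihood-ratio and profile-likelihood (Firth-penalised) inference from the Poisson model with only a few prespecified baseline covariates.

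Report the fuller covariate-adjusted model as secondary, with Firth penalisation and profile-likelihood intervals. Apply the same rule to the 6-month repeat, where an empty arm is three times as likely.

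The cost is one sentence and routine R code, with no extra participants or data. The downside is slight miscalibration at these counts: mid-P rejects about 4.5% under the null and the unpenalised likelihood ratio 5.4-6.4%. The Firth version was not calibrated here, so a short simulation should accompany it if chosen. The fully exact test is safe but conservative and should not be the first choice.

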### Objectives

The primary objective of this study is to assess the efficacy of VMMC for preventing HIV acquisition among MSM who primarily engage in insertive anal sex. The secondary objectives are to assess (1) the safety of and satisfaction with surgical VMMC among MSM; (2) changes in reported sexual risk behaviors after circumcision among MSM; and (3) the efficacy of VMMC for preventing sexually transmitted infections (STIs), including herpes simplex virus type 2 (HSV-2), syphilis, and penile HPV among MSM. Our hypothesis is that VMMC could reduce the risk of HIV infection among MSM.

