### Eligibility Criteria

Individuals who meet all of the following criteria are eligible for enrolment in the CoM Study: (1) aged 18-49 years; (2) assigned male sex at birth; (3) ≥2 male sex partners and ≥10 episodes of anal sex in the past 6 months; (4) practiced insertive role in ≥7 of the last 10 episodes of anal sex with male sex partners; (5) HIV negative; (6) has foreskin that covers over half the glans when the penis is not erectile; (7) is willing to undergo VMMC; (8) resides in the city where a study site is located and has no plan to relocate in the next 12 months; (9) is willing to provide a blood sample and exfoliated penile swabs to test for HIV, HSV-2, syphilis, and HPV; and (10) is able to provide informed consent. Men who are already circumcised or enrolled in other biomedical HIV intervention studies will be excluded. Men who have been diagnosed with a bleeding disorder or have other medical contraindications to VMMC will also be excluded.

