### Study Measures

The baseline and follow-up surveys will collect information on sociodemographic characteristics (including age, ethnic, educational background, marital status, and monthly individual income) and sexual behaviors (including the number of male and female sex partners, frequency of vaginal or anal sex, condom use, and HIV-positive sex partners) for all enrollment participants. Follow-up surveys will be completed at 6- and 12-month follow-ups. Men randomized to receive VMMC will also be asked to complete weekly follow-up surveys for 6 weeks after VMMC to monitor for postsurgical complications, including pain, poor surgical site wound healing or infection, and premature resumption of sexual behaviors. If an adverse event is reported, trained investigators will contact participants and provide advice on whether further clinical evaluation is needed.

Fingertip blood drop samples will be collected at baseline as well as 3-, 6-, 9- and 12-month follow-ups and tested for HIV using an HIV rapid test. Venous blood samples collected at baseline as well as 6- and 12-month follow-ups will be tested for HIV, syphilis, and HSV-2. Penile swab samples will be collected at baseline as well as 6- and 12-month follow-ups and tested for HPV.

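### The GEE for sexual-behavior change does not name the baseline value as a covariate; read as an unconstrained arm-by-time comparison, it gives up precision on secondary objective 2

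*Protocol article*

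**What the plan says.** Objectives lists as the second secondary objective "changes in reported sexual risk behaviors after circumcision among MSM". Statistical Analysis gives it one sentence: "The changes in sexual behaviors after VMMC over time between the intervention and the control groups will be compared with the generalized estimating equations". That sentence names no response vector, link, working correlation or covariate.

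Two neighboring statements in the same section bear on how to read it. The Poisson model for incidence has its covariates listed one by one, while the GEE has none. Baseline characteristics in general are to be carried into later analyses only if the arms turn out unbalanced on them.

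The baseline behavior values are collected. Study Measures says "The baseline and follow-up surveys will collect information on sociodemographic characteristics" and then names the behaviors: "the number of male and female sex partners, frequency of vaginal or anal sex, condom use, and HIV-positive sex partners". It adds that "Follow-up surveys will be completed at 6- and 12-month follow-ups". Each man can therefore have one baseline and two follow-up reports.

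**The concern.** The sentence names a quantity, change over time compared between arms. With three surveys the usual fit takes all three as responses and tests an arm-by-time term. When the arm and time effects are saturated, that term is a difference between arms in change from baseline. The chance error in each man's baseline report is then subtracted in full from his follow-up values and enters the treatment contrast.

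In a randomized trial the arms differ at baseline only by chance. Using the baseline value as a covariate removes only the part that predicts follow-up, and so gives a smaller variance from the same data.

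What is at stake is the chance of seeing a behavioral shift after circumcision. Limitations raises the possibility that recently circumcised men may move towards receptive sex and thereby raise their HIV risk. The sample size was set for HIV incidence alone ("A target sample size of 240 (120 in each group) is set to achieve 80% power at 1-sided α=.10, with 10% lost to follow-up"), so no power was reserved for behavior. A noisier contrast makes a real shift more likely to be reported as no difference.

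**Working it through.** **Figure to reproduce.** The article gives no SD, correlation, detectable difference or power for any behavior, so there is no figure of its own to reproduce. The 240 men are used below only for scale.

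**Inputs.** One baseline and two follow-up reports (Study Measures); 1:1 allocation ("Eligible men will be randomized using a 1:1 allocation ratio to the intervention and control groups"); 240 men with 10% loss, so 240 × 0.9 = 216 evaluable, 108 per arm (Sample Size). Assumed: equal variance of 1 at each survey and one correlation r between any two surveys (compound symmetry), with r = 0.3, 0.5 and 0.7.

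**Formulas, per man, for the mean of months 6 and 12.**
- Follow-up mean alone: (1+r)/2
- Change from baseline: (1+r)/2 + 1 − 2r = 1.5(1−r)
- Baseline-adjusted: (1+r)/2 − r²
- Ratio adjusted/change: (1+2r)/3

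| r | Follow-up only | Change | Adjusted | Ratio | Variance removed | SE reduction, 1 − √ratio |
|---|---|---|---|---|---|---|
| 0.3 | 0.65 | 1.05 | 0.56 | 0.53 | 47% | 27% |
| 0.5 | 0.75 | 0.75 | 0.50 | 0.67 | 33% | 18% |
| 0.7 | 0.85 | 0.45 | 0.36 | 0.80 | 20% | 11% |

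In numbers of men, 216 analyzed as change are worth about 216 × 0.533 = 115, 216 × 0.667 = 144 or 216 × 0.80 = 173 analyzed with adjustment.

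**One visit at a time.** Change is 2(1−r) and adjusted is 1−r², so the ratio is (1+r)/2. That gives 0.65, 0.75 and 0.85, or 35%, 25% and 15% of the variance removed.

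**Which r is likely.** The article does not say. Entry is selected on recent behavior ("≥2 male sex partners and ≥10 episodes of anal sex in the past 6 months"), which tends to lower the correlation and so raise the gain. This is an argument for plausibility, not an estimate.

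**Check by simulated GEE, 108 men per arm.**
- Continuous outcome, 250 runs per setting: adjustment removed about 43%, 35% and 13% of the variance at r = 0.3, 0.5 and 0.7. With so few runs this agrees with the formula. A GEE with a common baseline mean did as well as the baseline covariate.
- Counts with a log link, 400 runs, assumed effect: variance ratios 0.50, 0.63 and 0.74 at r = 0.18, 0.38 and 0.61. Mean estimates were nearly equal (for example 0.326 and 0.329). Power rose from 71%, 67% and 58% to 97%, 87% and 74%.
- Yes/no behavior as a risk difference, 400 runs, assumed effect: ratios 0.42, 0.53 and 0.63 at r = 0.13, 0.27 and 0.44. Power rose from 64%, 53% and 40% to 92%, 80% and 67%.
- Yes/no behavior with a logit link: the adjusted coefficient is conditional and larger. In one set of runs with r about 0.5 it averaged 0.70, against 0.54 for the change contrast, with a variance ratio of 1.14. Coefficient variances cannot be compared directly on this scale, although power still rose in a separate set of runs.

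**The case against.** The strongest objection is that the sentence does not fix a model. A GEE with a baseline covariate, or with a common baseline mean, would fit the same words, and the loss would then be about zero. How baseline enters a secondary GEE is often left to an analysis plan, which is not shown. This stands in part: a reader might infer that the article rules out baseline adjustment and is certain to waste precision, and it does not say so. But the sentence does name the contrast, lists no covariates where the Poisson model lists many, and sits beside a rule that brings in baseline characteristics only on imbalance. Asking for the baseline value to be named is therefore a concrete improvement to what is written.

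Four other inferences are tempting and not supported:
- **Change is the least precise use of the surveys.** By the table, that holds only for r below 0.5. At 0.5 change ties with the follow-up mean alone, and above 0.5 it is better.
- **Adjustment always estimates the same effect.** Not for odds ratios, as the logit runs show.
- **The article expects behavior to become riskier.** Limitations says only that it may.
- **Dropout will bias the planned contrast.** Dropout that depends on baseline behavior equally in both arms need not do so. Nothing in the article points to differential dropout, and Statistical Analysis plans to examine attrition.

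**Conclusion.** The point holds as a matter of efficiency on a secondary objective. If the GEE is fitted with baseline as a response and an unconstrained arm-by-time term, adjustment would remove roughly 20% to 47% of the variance of the two-visit average for r between 0.7 and 0.3, or 11% to 27% of the standard error. The size rests on an assumed correlation and on compound symmetry. It falls below 20% for r above 0.7 and exceeds 50% for r below 0.25. For counts and yes/no behaviors the linear formula is approximate, but the simulations point the same way on the log-count and risk-difference scales. The planned contrast is unbiased under randomization, and there is no loss if the intended model already conditions on or constrains baseline.

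**What to change.** Replace the GEE sentence with one to this effect: month-6 and month-12 behaviors will be compared between randomized arms by GEE with arm, visit, arm-by-visit and the participant's own pre-allocation value of that behavior as a covariate (or with a common baseline mean for both arms); the arm effect will be reported at each visit and averaged over visits. For yes/no behaviors, report a standardized (marginal) risk difference or ratio so that the estimand stays marginal. Within-arm change over time may still be described.

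The cost is a sentence or two and no new survey. One thing needs confirming: the covariate must have been recorded before allocation. The Abstract describes the baseline report ahead of random assignment, Table 2 puts both at month 0, and Randomization and Follow-Up has control men completing the baseline survey after enrollment. The plan should state the order.
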